---

## **GLOSSARY AND ABBREVIATIONS**

AE – Adverse Event

AFB – Acid Fast Bacilli

BU – Buruli Ulcer, Buruli Disease

CNS – Central Nervous System

CRF – Case Report Form

GCP – Good Clinical Practice

IMP - Investigational Medicinal Product

PCR – Polymerase Chain Reaction

SAE – Serious Adverse Event

ZN – Ziehl-Neelsen

## **KEYWORDS**

Buruli Disease, Wound Management, Wound healing

## SUMMARY OF INVESTIGATION AND ASSESSMENTS

Figure 1: Overview of the two study sites

[figure not shown]

[figure not shown]

Figure 2: Observational study phases and study groups in Obom

[figure not shown]

Figure 3: Observational study phases and study groups in Amasaman

|                                                                                                                  | Day0                    | Month 1                       | Month 2                      | Month 3                          | Month 4                          | Month 5                          | Month 6                          |
|------------------------------------------------------------------------------------------------------------------|-------------------------|-------------------------------|------------------------------|----------------------------------|----------------------------------|----------------------------------|----------------------------------|
| Clinical examination at enrolment                                                                                | X                       |                               |                              |                                  |                                  |                                  |                                  |
| Informed consent                                                                                                 | X                       |                               |                              |                                  |                                  |                                  |                                  |
| 
 
Clinical wound assessment
 
Weight
 
Temperature
 
 | X                       | Once a week and if indicated  | Once a week and if indicated | Every two weeks and if indicated | Every two weeks and if indicated | Every two weeks and if indicated | Every two weeks and if indicated |
| Photo documentation of wound                                                                                     | X                       | Every two weeks               | Every two weeks              | Every two weeks                  | Every two weeks                  | Every two weeks                  | Every two weeks                  |
| Swabs (ulcer) for diagnosis (PCR, AFB, culture, AG- test)                                                        | X                       |                               |                              |                                  |                                  |                                  |                                  |
| FNA (nodule) for diagnosis (PCR, AFB, culture, AG-test)                                                          | X           |                               |                              |                                  |                                  |                                  |                                  |
| Swabs (ulcer) for secondary bacterial infection and resistance testing                                           | X                       | after 2 weeks + after 4 weeks | If indicated                 | If indicated                     | If indicated                     | If indicated                     | X                                |
| Punch biopsy                                                                                                     | X                       |                               | X                |                                  |                                  |                                  |                                  |
| Blood test (WBC, differential, HIV-test  , sickle test  )                                | X                       |                               |                              |                                  |                                  |                                  |                                  |
| Blood test (WBC, differential, CRP, malaria, blood culture and others)                                           | If clinically indicated |                               |                              |                                  |                                  |                                  |                                  |

if clinically indicated punch biopsy at one additional later date

 additional biopsies if indicated and during surgery.

 if positive: CD 4 count, viral load, repeatedly if clinically indicated

 if positive: referral to a sickle cell disease centre

Table 1 Time schedule

# STUDY PROTOCOL

## 1 INTRODUCTION

### 1.1 Background

Buruli Disease (BU) is a chronic necrotizing disease of the skin and soft tissue caused by *Mycobacterium ulcerans* [1]. The disease starts as a subcutaneous nodule, papule or plaque that eventually ulcerates and progresses over months to years. The disease can affect all age groups, but children under 15 years of age are predominantly affected [2]. Serious permanent disability may result. *M. ulcerans* produces a macrolide toxin, mycolactone, which is associated with tissue destruction and local immunosuppression [3]. BU has been reported in >30 countries, but the major burden lies on children living in remote areas of West Africa associated with swamps and stagnant water bodies [4]. Over decades wide excision of the infected tissue was the standard treatment for BU. Disadvantages are the highly traumatic nature of the interventions, high cost and very high recurrence rates. Chemotherapy with streptomycin/ clarithromycin and rifampicin has successfully been tested in a recent trial and further trials are ongoing [5]. Chemotherapy has become an essential part of the treatment recommendations of the WHO BU Technical Advisory Group [6] and is currently implemented in BU endemic regions by national BU control program.

In the treatment of BU patients general wound management has been grossly neglected. The focus has been largely on the *M. ulcerans* specific anti-mycobacterial treatment. Problems of wound healing due to local immune reconstitution (paradoxical reactions) and intervening secondary bacterial infections have been misinterpreted and underestimated. Their impact on time to healing (wound closure) and morbidity is significant. This can only be reduced through improvement of general wound care on the basis of better knowledge of the underlying processes. Transferability of results generating in BU patients with chronic wounds to other types of wounds will be high.

### 1.2 Rationale for the study

To contribute to a better understanding of wound healing and to improve wound management in settings with limited resources, a prospective observational follow-up study of BU patients with chronic wounds will be conducted.

A specific focus will be to disentangle the three principle mechanisms which drive the wound pathology in otherwise healthy patients: (a) the mycobacterial infection, including remaining mycolactone levels in the affected tissue (b) local immune reconstitution and (c) secondary bacterial infections. On the basis of improved knowledge of these entities and their time course clinical recognition can be improved, rational laboratory diagnostics suggested and wound care procedures tailored to the needs and health care settings.

The study will be conducted in the Buruli Ulcer Ward at Amasaman Municipal Hospital and in the Health Centre of Obom. Studying patients in both facilities will allow comprehensive insight in the management and healing of Buruli Ulcer wounds at the primary and secondary level of the health care system.

## STUDY OBJECTIVES

### 1.3 Overall goal

To contribute to a better understanding of wound healing and to improve wound management in settings with limited resources at the primary and secondary level of the health care services.

### 1.4 Study objectives

- (1) To establish the clinical and laboratory tools for monitoring BU patients with chronic wounds.
- (2) To initiate a prospective cohort of BU patients with continuous enrolment at Amasaman District Hospital and Obom health Centre.
- (3) To describe BU lesions including secondary effects (secondary bacterial infections; local immune reconstitution; emergence of secondary lesions) at enrolment and over time until the wound is closed (or the 6 months study period is completed) for
  - A.) Hospital based setting
  - B.) Health Centre based setting
- (4) To investigate the microbiological, histopathological and immunological features including wound healing parameters at enrolment and over time until the wound is closed (or the 6 months study period is completed) for
  - A.) Hospital based setting
  - B.) Health Centre based setting

## 2 STUDY DESIGN

Prospective observational follow-up study of Buruli Ulcer patients treated in:

- A.) The Buruli Ulcer Ward at the Municipal Hospital of Amasaman
  - inpatients already hospitalized at day 0 ("old cases") ( $n_{OC}=30$ )
  - inpatients newly admitted ("new cases") during study period ( $n_{NC}=30$ )
  - outpatients ( $n_{OP}=20$ )
- B.) The Health Centre of Obom
  - outpatients ( $n_{OP}=50$ )

Study duration

2 years

### **3 PARTICIPANT ENTRY**

#### **3.1 Study Site and Target Population**

##### **3.1.1 Study Site**

The study will take place in

- A.) The Buruli Ulcer Ward at Amasaman Municipal Hospital (AMH) in the Ga West District of the Greater Accra Region
- B.) The Obom Health Centre (OHC) in the Ga- South Municipality of the Greater Accra region.

Both institutions are the main health care facilities that offer Buruli ulcer case management services in the respective district; both offer clinical diagnosis, wound dressing and Streptomycin/ Rifampicin treatment according to WHO recommendations, while AMH in addition has facilities for surgical excision and skin grafting. The two districts are the only districts that are BU endemic in the Greater-Accra Region and annually attend to more than hundred cases. The Ga-West Municipal Health Directorate reports the second highest number of BU cases in Ghana; furthermore it receives the worst cases nationwide. The Amasaman Municipal Hospital has both in-patient (consisting of three wards and 40 beds capacity) and out-patient facility while the Obom Health Centres has only out-patient facility. Both health care facilities have a longstanding collaboration with the Noguchi Memorial Institute for Medical Research (NMIMR), Legon, for case confirmation by PCR and also offer additional laboratory investigations when needed to support case management.

##### **3.1.2 Target Population**

BU patients of the Buruli Ulcer Ward / OPD at Amasaman District Hospital in the Ga West District of the Greater Accra Region and BU patients of the Health Centre at Obom.

#### **3.2 Inclusion Criteria**

- A.) In- and out-patients with confirmed BU lesions (ulcers / nodules) at Amasaman District Hospital.
- B.) Outpatients with confirmed BU lesions (ulcer/ nodules) at the Health Centre of Obom

#### **3.3 Exclusion Criteria**

Since no significant adverse effects are foreseen for patients participating in this observational study, no specific exclusion criteria are applicable.

### **3.4 Pre- enrolment Evaluation**

Patients fulfilling the inclusion criteria (see section “inclusion criteria” above) will be fully informed about the clinical study and informed written consent of patients or their representatives willing to participate will be obtained (see section 8.2).

All patients who have consented will be submitted to following pre-enrolment evaluations

- (1) Clinical evaluation of the ulcers following the WHO guidelines (WHO 2002)
- (2) Medical history
- (3) Full physical examination

Patients who are not enrolled will be receiving the same standard care as all patients of the Amasaman Buruli Ulcer Ward / OPD or the Health Centre of Obom.

### **3.5 Withdrawal Criteria, Procedures after Withdrawal**

Patients can withdraw at any time from the study and will continue to receive the standard care of the Amasaman Buruli Ulcer Ward.

## **4 ASSESSMENT AND FOLLOW-UP**

### **4.1 Clinical and Laboratory Assessments (at enrolment)**

A) Buruli Ulcer Ward at Amasaman Municipal Hospital

- Baseline clinical examination including photographic documentation
  - Overall clinical assessment (past and present medical history, present complaints, physical examination)
  - Description of the lesion (margin of ulcer, size of ulcer / nodule [max / min diameter, size in mm^2 determined in digital images taken in a standardized format], wound exudates, epithelialisation, scarring, temperature at lesion and contra lateral)
- Laboratory tests
  - Fine needle aspiration (nodules) for Buruli Ulcer diagnosis
  - Swab samples (ulcers) for diagnosis, validation of new diagnostic procedures and for the analysis of secondary infections and for further necessary analysis
  - Punch biopsies (ulcers) for assessment of histopathological features, nature and localization of secondary infections and for markers of inflammation and wound healing
  - Blood samples for WBC, differential, HIV- test, sickle test
  - Blood samples of patients if clinically indicated for blood cultures, malaria RDT, CRP

- Blood samples from HIV positive patients for CD4 count and viral load

B) Health Centre in Obom:

Same as above

## 4.2 Clinical and Laboratory Assessments during Follow up

Follow-ups are performed at the intervals as lined out in table 1:

A) Buruli Ulcer Ward at Amasaman Municipal Hospital

- Clinical examination and assessment
  - Clinical assessment (body temperature, weight)
- Assessment of wound healing and secondary effects
  - Description of the lesion ( size of ulcer / nodule [max / min diameter, size in mm^2 determined in digital images taken in a standardized format], epithelialisation, scarring, moisture balance, wound ground, granulation tissue, wound exudates, margin of ulcer, temperature at lesion and contra lateral, wound surface, odour, pus)
  - Photo documentation made of all lesions.
- Laboratory tests
  - Punch biopsies (ulcers) for assessment of histopathological features, nature and localization of secondary infections and for markers of inflammation and wound healing treatment success
  - Swab samples (ulcers) for analysis of secondary infections
  - Blood samples of patients with a temperature >38,5°C or clinically indicated for blood cultures, malaria RDT, WBC, differential blood count, CRP and others
  - Blood samples from HIV positive patients for repeated CD4 count and viral load
  - Tissue samples (of wound debridement, wound excision) for assessment of histopathological features

B) Health Centre in Obom: As above

All data will be directly entered into the CRF (source data)

## 4.3 Storage, Transport and Analysis of Samples (biopsies, swabs and blood samples)

Four swabs will be collected for investigating secondary infection; one will be used for direct smears for microscopic examination, the second inserted into a sterile tube containing 3 ml of PBS for

enumeration of bacterial load and isolation of specific aerobic pathogens, the third will be transported in Robertson's cooked meat medium for anaerobic bacteria isolation and the fourth will be used for cultivation of *M. ulcerans* and/or determination of mycolactone levels. Samples will be kept on ice and transported the same day to the laboratory at NMIMR for investigations the same day, if delay is anticipated, then samples will be collected into Amies transport media.

Biopsy samples for histopathological analysis will be inserted into 10% formalin for 24 hours, and then transferred into a new tube containing 70% ethanol, until analysis at Swiss Tropical and Public Health Institute in Basel, Switzerland. For the determination of mycolactone levels, biopsy samples will be immersed in chloroform/methanol and transported the same day to the laboratory at NMIMR for extraction.

Blood samples for microbiological analysis (for an adult, 10-15ml of blood is collected and 5ml for paediatric) will be collected directly into a diphasic blood culture bottles and transported within 24 hours to the laboratory for culture and isolation while blood for CD4 counts and viral load will be collected into vacutainer tubes (BD).

## **5 ADVERSE EVENTS**

The clinical observational study procedures do not pose any risk to the patient.

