## **6 STATISTICS AND DATA ANALYSIS**

### **Descriptive**

Simple descriptive statistics will be performed with baseline variables (age, sex) and wound healing related variables (clinical response, adverse events, histopathological, microbiological and immunological parameters and features).

1. Age and sex distribution of BU patients hospitalized/attending outpatient clinic in Amasaman and Obom
2. Residence of the BU patients attending the BU Centre Amasaman/ Obom
3. Nutritional status of BU patients
4. Frequency and types of skin diseases coexisting with BU
5. Frequency of BU lesions among relatives/ family members
6. Secondary bacterial infection/ colonization at hospital entry

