### **7.2 Consent**

Patients willing to participate in the study will be fully informed about the study procedures, the risks of participation and possible benefits. The explanation of the written English informed consent will be translated into the patient's spoken language when needed. In general, written informed consent will be obtained by the signature of the patient or the signature of the guardian/legal representative (in case a patient is minor) on the informed consent form or, if the patient or guardian/ legal representative is illiterate, certify their consent with a fingerprint accompanied by the signature of an impartial witness.

The right of the patient or guardian/legal representative to refuse participation without giving reasons will be respected.

All participants are free to withdraw their consent to participate in the study at any time without giving reasons and without any consequences.

The Ethics Committee(s) must approve the informed consent document to be used by the Investigator.

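### Section 5 calls the study procedures free of risk and sets up no adverse event recording, while ulcer biopsies are scheduled at Day 0 and Month 2 and Section 6 plans to describe adverse events

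*Protocol*

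**What the plan says.** Under its Adverse Events heading, Section 5 of the protocol has a single sentence: "The clinical observational study procedures do not pose any risk to the patient". Its only subsection, 5.1, describes laboratory methods, and the table of contents lists nothing else there. AE and SAE are spelled out in the glossary but not defined operationally in the text available.

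Section 6, under Descriptive, nevertheless names adverse events among the "wound healing related variables (clinical response, adverse events, histopathological, microbiological and immunological parameters and features" that are to be summarised.

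The study takes tissue from the ulcer being followed:

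- Section 4.1, at enrolment: "Punch biopsies (ulcers) for assessment of histopathological features, nature and localization of secondary infections and for markers of inflammation and wound healing".
- Section 4.2, during follow-up: "Punch biopsies (ulcers) for assessment of histopathological features, nature and localization of secondary infections", and also "for markers of inflammation and wound healing treatment success".
- Table 1 marks punch biopsy at Day 0 and at Month 2. The Month 2 mark carries a footnote: "additional biopsies if indicated and during surgery".

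Section 7.2 says that patients will be "fully informed about the study procedures, the risks of participation and possible benefits".

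**The concern.** A punch biopsy removes tissue, so a flat statement of no risk does not fit a schedule that includes it. The statistical problem follows from this. Section 6 plans to describe a variable for which the protocol defines no event, no collection and no attribution. If few or no adverse events are reported, the reader cannot tell whether none occurred or none were asked about.

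The biopsy site also lies in the wound whose course is the subject of the study. The Analytical part of Section 6 plans to examine wound size over time, secondary infection or colonisation over time, pain during healing, and patient factors behind infection and delayed healing. A local complication of the biopsy could enter any of these as disease course or as a secondary infection, with nothing in the data to mark it as a procedure effect.

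**Working it through.** The protocol gives no figure to reproduce here. The check compares its sections and makes one count.

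**1. Is there any adverse event collection?**
- Section 5: one sentence on risk, then laboratory methods.
- Table 1: rows for examination, consent, wound assessment, photographs, swabs, aspirates, biopsy and blood tests. There is no adverse event row.
- Section 4.2: clinical assessment, wound description, photographs and laboratory tests. There is no adverse event item.
- Section 6: adverse events are listed as a variable to be described.

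The variable is therefore planned for summary without a stated source.

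**2. Are the biopsies part of usual care or added by the study?** Section 3.1.1 describes care at the two sites: "both offer clinical diagnosis, wound dressing and Streptomycin/ Rifampicin treatment according to WHO recommendations". The hospital also offers excision and skin grafting. Serial biopsies are not mentioned. Sections 4.1 and 4.2 give the biopsies' purpose as histopathology, the site of secondary infection, and markers of inflammation and healing, while diagnosis is assigned to swabs and aspirates. That the study adds the scheduled biopsies is a reasonable inference, but the protocol does not say so outright.

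**3. How many biopsies?** Section 2 gives the planned groups.
- Patients: 30 + 30 + 20 + 50 = 130.
- Scheduled biopsies per ulcer patient: 2 (Day 0 and Month 2).
- Ceiling: 2 × 130 = 260.

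The ceiling assumes that every patient has an ulcer that is still open, and is still followed, at Month 2. Section 3.2 admits nodules, and biopsies are specified for ulcers, so the true number will be lower. If the Month 2 footnote means that this biopsy is itself conditional, the scheduled ceiling falls to 1 × 130 = 130. Unscheduled biopsies come on top in either case.

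**4. What would the existing record catch?** Section 4.2 records ulcer size, margin, exudate, odour, pus, lesion temperature and body temperature in the CRF. Table 1 places wound assessment weekly in Months 1 and 2 and every two weeks afterwards. Infection swabs are scheduled 2 and 4 weeks after enrolment, then only if indicated until Month 6.
- Likely to leave a trace: enlargement, local infection, fever, slow healing.
- No stated place: bleeding at the procedure.
- Missing for all of them: relation to the biopsy, and any label as an adverse event.

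**5. Do the risk statements agree?** Section 5 says there is no risk. Section 7.2 presupposes risks to be explained. The schedule contains an invasive procedure. Section 5 cannot stand unchanged beside the other two.

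**The case against.** The strongest reply is that data do exist. The wound is examined often and in detail, and blood cultures are taken for fever. Section 6 lists adverse events as a wound-healing variable, so the term may mean the secondary effects that Sections 1.4 and 4.2 already track. This stands in part. A reader might infer that complications would go entirely unrecorded, and the protocol does not support that. What is missing is attribution, labelling, and a place for events that the wound description does not cover. Nor does the protocol say that the secondary effects are the adverse events meant in Section 6.

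A second reply is that the Section 5 sentence may refer only to clinical observation. If so, the adverse events section does not deal with the sampling procedures at all, and the gap remains. Adverse event text may also sit in Section 8 (Study Management), which was not available for this review. Even so, it would not remove the conflict between the Section 5 sentence and the scheduled biopsies.

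Three further inferences are tempting but go too far:

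- That Section 3.3 waives exclusion criteria on the same no-risk premise. It says only that no significant adverse effects are foreseen, which is weaker and compatible with a minor biopsy risk.
- That aspiration and all blood sampling are done for the study. Aspiration is for diagnosis, and most follow-up blood is drawn for fever, on clinical indication or for HIV monitoring. The point rests on the scheduled biopsies.
- That a number of lost events can be given. The documents contain no complication rate, and multiplying an assumed one by a ceiling would not be informative.

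The Section 7.2 wording is also usual consent language. Its conflict with Section 5 is real but secondary.

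**Conclusion.** The point holds as an internal contradiction about the scheduled biopsies and the planned adverse event summary. It is not merely detail left to an analysis plan: such a plan can summarise adverse events, but their definition and collection belong in the protocol, and the section reserved for them says instead that there is no risk.

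In size, it concerns at most 260 scheduled biopsies in 130 patients, or at most 130 if the Month 2 biopsy is conditional. Nodules and early closure lower both figures. The number of complications involved cannot be estimated from the documents.

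The consequence is limited but definite. An empty or sparse adverse event table would be uninterpretable, and biopsy effects could blend into the healing and infection results. The conclusion assumes that the scheduled biopsies are added by the study, as their stated purpose suggests, and that the unavailable Section 8 contains no adverse event procedure. If either assumption fails, the point becomes smaller, but the Section 5 sentence would still need correction.

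**What to change.** - Reconcile Sections 5, 6 and 7.2 with the biopsies in Table 1 and Sections 4.1 and 4.2.
- Replace the no-risk sentence in Section 5 with a short statement of the foreseeable risks of the study's procedures.
- State in Section 5 what counts as a procedure-related adverse event, and record each one on the CRF at the existing visits, with type, onset date and relation to a biopsy.
- State in Section 6 that the adverse event summary draws on these records, and whether the secondary effects in Section 4.2 count as adverse events.

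The cost is a short amendment and one CRF page, with no extra visits or samples.
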